#### Validation of existing SARS-CoV-2 antigen and serological assays could enhance case-finding and surveillance of COVID-19 in sub-Saharan Africa

The limited laboratory capacity for SARS-CoV-2 molecular testing and the global stock-outs of reagents raised interest on using rapid and/or easy-to-use devices to facilitate screening in SSA, based either on SARS-CoV-2 antigen detection in sputum/throat/swab samples, or human antibodies detection in blood/sera/plasma specimens [17, 18]. However, the performance of these rapid assays remains largely unknown within SSA populations. Rapid antigen tests are designed to detect the presence of a viral antigen (targeting usually the Nucleocapsid), and the tests are inexpensive, easy to use, have short turn-around time, suitable for point-of-care (PoC), but with a lower diagnostic sensitivity (provide reliable results only with high viral-loads ≥100,000 copies/mL) especially during the first days after symptoms onset [19–21]. Due to this limitation, WHO, CDC and ECDC recommend the use of rapid antigen tests with a subsequent confirmation of negative results by RT-qPCR [22–24]. Among the 3rd generation antigen-detecting tests LumiraDx, Panbio COVID-19 Abbott Ag Rapid Test and Standard Q COVID-19 Ag Test Biosensor comply with the minimum performance requirements of the WHO [23].

Regarding serological assays, performance varies according to manufacturers (https://www.fda.gov/medical-devices/coronavirus-disease-2019-covid-19-emergency-use-authorizations-medical-devices/eua-authorized-serology-testperformance); FDA recommended antibody tests with highest performance are Abbott Architect SARS-CoV-2 IgG (100% sensitivity, 99.6% specificity), Abbott Laboratories Advise Dx SARS-CoV-2 IgM (95.0% sensitivity, 99.6% specificity), Assure Tech. Assure COVID-19 IgG/IgM Rapid Test Device (100% sensitivity for IgM and 90.0% for IgG; 98.8% specificity for IgM and 100% for IgG) and the EUROIMMUN SARS-COV-2 ELISA IgG (90.0% sensitivity and 100% specificity). Among them, Abbott ARCHITECT SARS-CoV-2 IgG assay showed a satisfactory performance, with excellent sensitivity and specificity after 14 days of sympthom onset [25–27]. The availability of neutralizing antibody detection kit, such as the approved GenScript cPass SARS-CoV-2 Neutralization Antibody Detection Kit (100% sensitivity and specificity) allows the discrimination of neutralizing antibodies at population level [26, 27].

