### Specific objectives

**To integrate and improve the available infrastructure, methodologies, and expertise on COVID-19**. For this purpose, we will create a platform enabling researchers and clinicians to better integrate and coordinate their research and translate the project outcomes into scientific and clinical expertise for the management of COVID-19 infection within the African context;**To enhance the capacities of the involved centers in Cameroon to screen and detect individuals at risk for COVID- 19 infection, by putting in place effective screening mechanisms and facilities at core sites (based on molecular and serological detection methods and SARS-CoV-2 genome sequencing)**. In this frame, individuals will be considered at risk of COVID-19 infection according to surveillance case definition for human infection with novel coronavirus published by WHO [WHO/COVID-19/Surveillance/v2020.2, January 15 2020];**To determine the performance of sensitive and specific point-of-care molecular detection assay for SARS-CoV-2**. Previous data on Zaire Ebola virus suggested that the POC molecular test has comparable diagnostic accuracy to the conventional real-time, minimized the time to obtain a result, thereby allowing clinicians or public health staff to make expeditious decisions. In the COVID-19 case, nasopharyngeal and oropharyngeal swab, and saliva will be valid samples to obtain a rapid and non-invasive screening for all travelers arriving in Cameroon. Concordance with other molecular tests already available for COVID-19 will be assessed (Corman et al. 2020; Chu et al. 2020);**To apply a rapid and sensitive ddPCR-assay SARS-CoV-2 quantification method as complementary to the standard RTPCR for COVID-19 diagnosis**. This test (single-step ddPCR assay) will have the ability to detect SARS-CoV-2 genome at very low copies number, representing a chance to detect infected subjects before any symptom onset, and to reveal the presence of COVID-19 in the environment in close contact with infected individuals. Based on ddPCR, a linear evaluation of SARS-CoV-2 load will be also available;**To validate a large panel of serological assays to identify COVID-19-exposed or vaccinated persons and to follow-up of COVID- 19 convalescents or immunisation**. This panel will enable an appraisal of Nucleocapside (N) and Spike protein (S) used in screening for natural and artificial immunity respectively;**To evaluate the variability of circulating SARS-CoV-2 variants in Cameroon based on whole genome sequencing and phylogenetic approaches**. Through sequencing of SARS-CoV-2, evidence on the dynamics of COVID-19 from the lineage of origin to newly emerging variants will be delineated, with the goal in predicting the trends of SARS-CoV-2.

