#### Serological and antigen testing of COVID-19 suscepted cases: Antibody-based testing

For now, there are about five antigen-detection RDTs and 27 antibody-detection RDTs that have been selected for the first round of evaluation worldwide (and more are in evaluation), following approvals by FDA and EUA, and consideration for assessment by the Foundation for Innovative New Diagnostics (FIND), available at https://www.finddx.org/covid-19/sarscov2-eval-immuno/.

Based on preliminary results on 100 samples, five most efficient commercially available serological tests (Elisa tests: Dia.Pro COVID-19 IgG/M + confirmation and Aliphax WANTAI SARS-CoV-2; CLIA: Diasorin CLIA LIASON SARS-CoV2SI/S2 IgG; Rapid: Aliphax Cellex q Rapid Test; VivaDiag COVID-19 IgM/IgG rapid Test) were selected, with sensitivity and specificity ranging between 75%-98%. Antigen detection tests to be evaluated are LumiraDx Ag, Panbio COVID-19 Abbott Ag Rapid Test and Standard Q COVID-19 Ag Test Biosensor. Based on local neeeds, INDICAID AgRDTs (Phase Scientific), Ninonasal AgRDTs (NG. BIOTECH Laboratories) and NG.TEST/IgG-IgM COVID-19 (NG. BIOTECH Laboratories) could be considered.

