#### Statistical analysis

Data will be collected on standard tools (S3 File) by trained field epidemiologists and stored in a password-protected database to ensure confidentiality of participant data and their privacy at the local institution in Yaoundé-Cameroon, by experienced statisticians who will coordinate data management and analyses using SPSS software, according to Good Clinical Data Management Processes (GCDMP).

Diagnostic Performance will be evaluated regarding the sensitivity, specificity, positive/negative predictive values (with 95% Confidence Intervals) will be described using ddPCR as molecular gold standard assay (lower detection limit of 10 copies/test) and ELISA as serology gold standard, stratified by range of viral loads, Ct values, duration after symptom onset, target biomarkers and viral diversity. To provide the highest level of evidence, adjustments of confounders (age, gender, HIV status, onset of symptoms, site, etc) will be performed using logistic and linear regression, wherever applicable.

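### Serological accuracy is judged against an unnamed ELISA treated as error-free, although two ELISAs sit in the tested panel and the protocol's own figures cap the panel at 98%

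*Protocol article*

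**What the plan says.** The Statistical analysis section sets two references for sensitivity, specificity and predictive values: ddPCR for the molecular tests and "ELISA as serology gold standard". It gives no product, target antigen or isotype for the ELISA. Results are to be stratified by, among other things, time since symptom onset and target biomarker.

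The section on serological and antigen testing selects five antibody tests: "Elisa tests: Dia.Pro COVID-19 IgG/M + confirmation and Aliphax WANTAI SARS-CoV-2", one CLIA and two rapid tests. They are described as "with sensitivity and specificity ranging between 75%-98" per cent, and the selection is "Based on preliminary results on 100 samples". The range is not split by test or by measure.

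The Specific objectives include "To validate a large panel of serological assays to identify COVID-19-exposed or vaccinated persons", with nucleocapsid (N) assays for natural immunity and spike (S) assays for artificial immunity. The Main objective and the Expected outcomes are narrower: they speak of serological rapid kits and of antibody rapid tests.

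No section gives the ELISAs a different reference, defines a composite reference, or corrects for an imperfect one.

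**The concern.** A reference standard is scored as if it made no errors. Here the reference is a class of assay that also appears in the list of tests, and the protocol itself reports that no test in the list exceeds 98%. Two problems follow.

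- **Imperfect reference.** A truly seropositive person missed by the ELISA counts as a false positive for any assay that detects the antibody. A false positive of the ELISA counts as a miss for any assay that is correctly negative. This holds whichever tests are evaluated.
- **Self-comparison.** If one of the two panel ELISAs is the reference and is also reported as an evaluated test, it scores 100% on both measures by construction. The second ELISA would be judged against the first.

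Which ELISA is used also matters. The Introduction reports ELISA positivity from day 15 after onset of 100% for total antibody, 94% for IgM and about 80% for IgG, so an ELISA of unstated isotype could be any of several references. Because N and S assays are meant to answer different questions, a reference with a different target from the test would turn genuine N/S differences in vaccinated people into apparent errors.

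At stake is the ranking of antibody assays that the Expected outcomes promise to policy-makers. As planned, it would partly measure resemblance to the chosen ELISA.

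**Working it through.** **Plan's own figure.** The 75% to 98% range cannot be reproduced: the document gives no counts per test and does not say what the 100 preliminary samples were judged against. It is used below only as a stated range.

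**Inputs**
- Reference sensitivity and specificity (SeR, SpR): both ends of the pooled range (serological testing section), and 90%/100%, from "EUROIMMUN SARS-COV-2 ELISA IgG (90.0% sensitivity and 100% specificity" in the Introduction. That last ELISA is not one of the selected tests.
- Seropositivity p: not given. Two stated positivity rates serve as stand-ins: 51% (Sample size) and 20.39% (Description of the Cameroonian settings). Equating either with seropositivity is an assumption.
- Index test: taken as perfect, so that every apparent error comes from the reference.
- Planned N: 1,536 (Sample size).

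**Formulas** for a perfect index test
- Apparent specificity = (1 − p)·SpR / [(1 − p)·SpR + p·(1 − SeR)]
- Apparent sensitivity = p·SeR / [p·SeR + (1 − p)·(1 − SpR)]

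**Apparent specificity at p = 0.51**
- 98%/98%: 0.4802 / (0.4802 + 0.0102) = 97.9%
- 90%/100%: 0.4900 / (0.4900 + 0.0510) = 90.6%
- 75%/98%: 0.4802 / (0.4802 + 0.1275) = 79.0%

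**All results for a perfect assay**

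| Reference SeR/SpR | Specificity, p = 51% | Sensitivity, p = 51% | Specificity, p = 20.39% | Sensitivity, p = 20.39% |
|---|---|---|---|---|
| 98%/98% | 97.9% | 98.1% | 99.5% | 92.6% |
| 90%/100% | 90.6% | 100% | 97.5% | 100% |
| 75%/98% | 79.0% | 97.5% | 93.9% | 90.6% |
| 75%/75% | 74.2% | 75.7% | 92.1% | 43.5% |

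**As counts.** True positives relabelled as false positives are N·p·(1 − SeR). At p = 0.51 this is 1,536 × 0.51 × 0.02 ≈ 16, 1,536 × 0.51 × 0.10 ≈ 78, or 1,536 × 0.51 × 0.25 ≈ 196.

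**Not perfect, same pattern.** For an index test that is itself 98%/98% at p = 0.51, the general formula with conditionally independent errors gives an apparent specificity of 96.0% against a 98%/98% reference and 77.9% against 75%/98%.

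**Self-comparison.** Whatever SeR and SpR are, the reference judged against itself gives 100%/100%.

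**The case against.** The strongest reply is that ELISA may be meant purely as comparator. The Main objective and the Expected outcomes name rapid kits and rapid tests, and the Abstract mentions ELISA separately from antibody-based kits. On that reading nothing is scored against itself. This stands as a real ambiguity. A reader might infer that the protocol plans to score the reference ELISA against itself, but no section says so. The objective to validate a panel of assays and the listing of both ELISAs among the selected tests only point that way. The imperfect-reference bias is present on either reading.

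A reader might also infer that the ELISAs have a stated accuracy as low as 75%. They do not: 75% is the lower end of a range pooled over five tests and two measures, and a rapid test could account for it. What stands is the ceiling of 98%, which applies to every selected test.

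Nor do the assays quoted in the Introduction show that this study's reference is worse than the tests it judges. Neither the 90%/100% ELISA nor the antibody assay credited there with 100% sensitivity is among the five selected.

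The plan also has partial safeguards: stratification by time since onset and target biomarker, overall agreement as an outcome, and adaptation to future WHO guidance. Stratifying divides the results but leaves the reference unchanged within each stratum.

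Finally, a journal article may leave the product name to the full protocol. That is fair for the name. It does not cover the stated choice to treat ELISA as error-free and to report sensitivity and specificity against it.

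**Conclusion.** The point holds in a limited form. The article fixes ELISA as the error-free serological reference, while its own figures say that no selected test, ELISAs included, exceeds 98%. Apparent accuracy of the other assays is therefore biased in both directions described above.

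The size is unknown. At 51% seropositivity, a perfect assay's apparent specificity runs from 97.9% (98%/98% reference), a small loss, through 90.6% (90%/100%) to 79.0% (75%/98%). The last shows what the stated range permits, not what the document says about an ELISA. At 20.39% the corresponding figures are 99.5%, 97.5% and 93.9%, but there even a 98%/98% reference lowers apparent sensitivity to 92.6%.

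These figures assume that seropositivity equals the stated positivity rates, that the index test is perfect and that errors are conditionally independent. Assays that tend to err on the same sera would show a smaller loss. The 100% self-score is conditional: it arises only if the reference ELISA is also reported as an evaluated test.

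**What to change.** 1. Name the comparator ELISA with its target antigen and isotype, and remove it from the list of evaluated tests.
2. Report comparisons with it as positive and negative percent agreement, within matching N or S target and vaccination status. The calculation is the same as for sensitivity and specificity, but the label no longer claims that the ELISA is the truth.
3. Take serological sensitivity primarily in RT-PCR/ddPCR-confirmed participants, by days since symptom onset. The Statistical analysis section already has this stratifier.
4. State in the Main objective and the Expected outcomes whether the second ELISA and the CLIA are evaluated tests or only the rapid kits are.

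**Cost.** Wording changes and a modest amount of extra analysis on specimens and assays already planned. The design is cross-sectional, and the Introduction puts median nasopharyngeal shedding at about 12 days, so the late-onset confirmed subset may be small and its intervals wide. It may also over-represent severe disease, since the Introduction says that most severe cases stay positive beyond day 10 while 90% of mild cases do not. True specificity is not estimated without an independent set of known negatives, and the report should say so.

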Validation of these SARS-CoV-2 RDTs in SSA populations/settings is of paramount importance for optimal clinical use and positioning. On one hand, antigens are expressed only when the virus is actively replicating (greater performance during acute/early infection), while false-positive results could occur if strips recognize viral antigens from other human-coronaviruses [17]. Thus, validating the use of antigen RDT would reduce events of false negative-results, ensure rapid identify of cases, and minimise the need for expensive molecular testing [17]. On the other hand, COVID-19 antibody-tests might be convenient mainly during recovery as antibody response often occur in the second week post-infection or immunisation. Consequently, antibody testing might lead to delayed clinical-intervention or transmission-prevention [28, 29]. Moreover, COVID-19 antibody test might have cross-reactivity with other human-flu and/or coronaviruses, and the strength/breath of antibody response might vary with age, nutritional status, disease-severity, therapeutic-interventions, or infections like HIV or immunodeficiency-associated comorbidities [30]. Using an enzyme-linked immunosorbent assay (ELISA), Zhao *et al*. showed high rates of seroconversion based on total antibody (93%), IgM (83%) and IgG (65%), with seroconversion time ranging from 11–14 days [11]; the presence of antibodies rapidly increased to 100% (total antibody), 94% (IgM) and ~80% (IgG) as from 15 days after symptoms onset. These are consistent with evidence from Tan *et al*., revealing that anti-nucleocapsid-IgM starts on day-7 and peaks on day-28, while IgG ranges from day-10 to day-49 [11]. Interestingly, combining RNA and Antibody testing might improve the overall sensitivity for detecting COVID-19 case, pending confirmatory findings in real-life situations [11].

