**Fig 2 pone.0273818.g002:**
[figure not shown]
Standard algortihm for routine COVID-19 testing in Cameroon. COVID-19: Coronavirus Disease 2019.

**Study reference site: Virology Laboratory of CIRCB** (http://www.circb.cm/btc_circb/web/) The “Chantal BIYA” International Reference Center for research on HIV/AIDS prevention and management (CIRCB) is a government institute of the Ministry of Public Health established on February 2006, of conducting research and clinical monitoring of HIV and co-infections/comorbidities, with compliance to QC/QA and proficiency testing. CIRCB is a WHO-Candidate as National HIV Drug Resistance Reference laboratory, providing technical support for viral-sequencing (PHIA survey, etc) and training of health-professionals. CIRCB has a biobank dedicated for the storage of well characterised infectious samples collected from heath facilities and within research projects, in accordance with GCP and ethical regulations. The standard operational procedures (SOP) for the biobanking are available at www.circb-cm/LBIOSOP-English (English version) and www.circb-cm/LBIOSOP-French (French version). Samples collected are plasma, serum, buffy-coat, blood, DNA, RNA, proteins, PBMCs, tissues, smears, saliva/sputum, infectious pathogens (HIV, HBV, HCV, HPV, etc). In response to COVID-19, CIRCB is a reference laboratoriy for SARS-CoV2 testing, a member of the National COVID-19 public health operations centre, a member of the national COVID-19 genomic surveillance plateform, and a member of the scientific taskforce for COVID-19 in the country.

**Study duration**: The study will run for a duration of two years, with an active enrolment phase during the first 6 months of the project, and subsequent laboratory analyses.

**Sampling method**: A consecutive non-randomised sampling strategy will be used for participants enrollment;

**Target population**: Individuals visiting our routine sample collection site for COVID-19 screening within the framework of the established laboratory network in place, CIRCB being the study reference laboratory.

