### Eligibility criteria

**Inclusion criteria**: Every individual found in Cameroon at the moment of the study, suspected/contact COVID-19 case as defined by the WHO, aged 21 years and above, and provide a written informed consent for participation;

**Non-inclusion criteria**: Suspected case without clinical data, any suspected case managed out of the country guidelines, or any suspected case without blood/respiratory fluid specimen available;

**Exclusion criteria**: Enrolled participant with neither results of real-time PCR, serological testing, nor SARS-CoV2 sequence data following positive-PCR for the respective analysis.

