#### Establishment of well-characterised respiratory and sera specimens of COVID-19 positive cases

Training of staffs on sample collection procedure, transportation, storage and monitoring conditions will be done as previously described by Wang et al., 2020 [6]. Specimens of oropharyngeal and nasopharyngeal specimens, whole blood/serum, will be collected by trained staffs of the CIRCB in Cameroon.

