### Ethical considerations

The present study will be conducted according to the declarations of Helsinki on ethical principles for medical research involving human subjects. (http://www.wma.net/en/30publications/10policies/b3/) Ethical clearance has been obtained from the Cameroon National Ethics Committee for Research on Human Health in Cameroon (http://www.cameroon-ethics.cm/fr/quisommesnous), under the reference N°2022/01/1430/CE/CNERSH/SP of January 20, 2022. Participants will provide their signed written informed-consent (see S1 and S2 Files), for illerate participants a fingerprinting system will be used alongsdide a translator whenever necessary; phlebotomy will be done by well trained personnel (venipuncture, oro/nasopharyngeal swabs) and performed by trained-staffs Privacy and confidentiality will be ensured, through the use of unique identifiers and a protected database. Laboratory results will be free of charge for clinical management whenever necessary. A data safety and monitoring will ensure for an appropriate monitoring of the study implementation, under the scientific advisory board of the CIRCB.

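### Antibody-test specificity, computed in suspects and contacts against ELISA with no known-unexposed sera, is agreement with ELISA rather than specificity for exposure, and its bias can go either way

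*Protocol article*

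**What the plan says.** The source of the sera and the reference standard are both stated.

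- **Who gives serum.** Under Eligibility criteria, a participant must be a "suspected/contact COVID-19 case as defined by the WHO, aged 21 years and above". The target population under Study design is "Individuals visiting our routine sample collection site for COVID-19 screening". Blood or serum is taken from each eligible participant at enrolment.
- **Reference.** The Statistical analysis section computes sensitivity, specificity and predictive values with "ELISA as serology gold standard". It does not name the ELISA kit.
- **Characterised panel.** The only one with a procedure section of its own is headed "Establishment of well-characterised respiratory and sera specimens of COVID-19 positive cases". No pre-pandemic, known-unexposed or other-coronavirus panel is mentioned.
- **Risk acknowledged.** The Introduction warns that a "COVID-19 antibody test might have cross-reactivity with other human-flu and/or coronaviruses".
- **Use of the result.** Expected outcomes lists specificity of antibody rapid tests for detection and epidemiological surveillance. It also promises assays suited to assessing exposure or immune response.
- **Tests.** Five serological tests were chosen after preliminary work on 100 samples, and two of them are ELISAs. Their sensitivity and specificity are given as 75% to 98%.

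**The concern.** An ELISA for SARS-CoV-2 antibody is itself an antibody test and is open to the cross-reaction that the Introduction describes. Used as the gold standard, it misclassifies in two ways. An unexposed person who reacts falsely on both assays is scored as a true positive of the index test. An exposed person whose antibody the ELISA misses but the index test finds is scored as a false positive of the index test. Only index-only false reactions are scored correctly.

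Suspects and contacts are not known negatives. Some may have been infected before, and Specific objectives expects vaccinated persons among those to be identified. A negative swab does not show that someone was never exposed. The planned regression adjustment for HIV status and other factors does not help, because the error sits in the reference result.

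At stake is the figure that would guide the choice of antibody tests for sero-surveillance. Read as specificity for exposure, it could lead to a poor test being adopted or a good one being rejected.

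**Working it through.** **Plan's own figures.** None is stated for antibody specificity or for a number of unexposed sera. The sample-size formula concerns SARS-CoV-2 positivity: 1.96² × 0.51 × 0.49 / 0.05² = 384.0. This reproduces but does not bear on the point.

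**Inputs, all assumed.** The documents give no local cross-reaction rate, exposure share or accuracy for the reference ELISA.

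- Shared false reaction in unexposed people: s = 5%.
- Index-only false reaction: a = 1%. No ELISA-only false reaction.
- Exposed share: p = 20%, 51% or 80%. The 51% borrows the positivity used in the sample-size section; it is not a seroprevalence.
- ELISA sensitivity: E = 100% or 95%. Index sensitivity: R = 90%. The values 95% and 90% lie within the quoted 75% to 98%.
- Misses in exposed people are independent between assays.

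**Formulas.**

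- True specificity = 1 − s − a = 1 − 0.05 − 0.01 = 94.0%.
- Apparent specificity = 1 − [(1−p)a + p(1−E)R] / [(1−p)(1−s) + p(1−E)].

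**ELISA misses nothing (E = 100%).** The exposed share cancels, leaving 1 − a/(1−s).

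- s = 5%: 1 − 0.01/0.95 = 98.9%, against a true 94.0%.
- s = 10%: 1 − 0.01/0.90 = 98.9%, against a true 89.0%.

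True specificity falls by five points while the apparent figure does not move. The shared part is invisible.

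**ELISA sensitivity 95%, s = 5%.**

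| Exposed | Index+ and ELISA− | All ELISA− | Apparent specificity | True |
|---|---|---|---|---|
| 20% | 0.008 + 0.009 = 0.0170 | 0.760 + 0.010 = 0.7700 | 97.8% | 94.0% |
| 51% | 0.0049 + 0.02295 = 0.02785 | 0.4655 + 0.0255 = 0.4910 | 94.3% | 94.0% |
| 80% | 0.002 + 0.036 = 0.0380 | 0.190 + 0.040 = 0.2300 | 83.5% | 94.0% |

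The figure is too high at 20% exposed, about right by coincidence at 51%, and far too low at 80%.

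**If misses are fully shared.** Suppose the index test also misses everyone whom the ELISA misses. The term p(1−E)R then drops out of the numerator. Apparent specificity becomes 1 − 0.0049/0.4910 = 99.0% at 51% exposed and 1 − 0.002/0.2300 = 99.1% at 80%. The direction depends on quantities that this sample cannot supply.

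**What a known-negative panel would give.** Every reactive result in such a panel is a false positive, whether or not the ELISA reacts too. Wilson 95% intervals, with q the observed proportion negative: [q + z²/2n ± z√(q(1−q)/n + z²/4n²)] / (1 + z²/n).

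- 196 of 200 negative: (0.98 + 0.0096)/1.0192 = 0.971, half-width 0.021, so 95.0% to 99.2%.
- 294 of 300 negative: 95.7% to 99.1%.

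**The case against.** The main objective is performance among individuals tested for COVID-19, which is the group enrolled. Cross-reactivity is a background remark and is not a listed objective or outcome. The tests span ELISA, CLIA and rapid formats with both N and S targets, and results are to be stratified by target biomarker, so complete sharing of false reactions is not a given. Index-only false reactions remain visible. The article is condensed: the 100 preliminary samples may have included known negatives, a full protocol could describe a negative panel, and Expected outcomes says the assay-evaluation protocols will follow future WHO guidance.

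Much of this stands as a limit on size. It does not remove the point. Sample and reference are both fixed in the text, the preliminary samples are not part of the planned analysis, and a general commitment to WHO guidance does not commit to a negative panel. Enrolling the intended users does not turn agreement with another antibody test into specificity for exposure.

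A reader might go further in three ways that the documents do not support.

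- **Specificity will usually look too good.** This needs an ELISA that misses almost nothing, or misses shared with the index test. The quoted 75% to 98% covers the two listed ELISAs and gives no ground for assuming the first.
- **The study can show no cross-reaction at all.** Only the part shared with the ELISA is hidden.
- **Sera are known to date from 2022.** The ethics clearance is "N°2022/01/1430/CE/CNERSH/SP of January 20, 2022" and enrolment is described "with an active enrolment phase during the first 6 months of the project", but no enrolment date is printed. The point does not depend on the year.

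**Conclusion.** The point holds as one about what is being estimated. The planned figure is agreement with an unnamed ELISA and should not be read as specificity for exposure. Under the assumed rates, a test with true specificity 94% could be reported anywhere from 83.5% to about 99%, depending on the exposed share, the ELISA's sensitivity and how far misses coincide. The documents support no net direction. These values illustrate the possible size and do not predict the study's result. The matter affects the antibody-test outcomes only; the molecular comparisons against ddPCR are untouched.

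**What to change.** 1. In Statistical analysis and Expected outcomes, report the participant comparison as positive and negative percent agreement with ELISA, and do not present it as specificity for exposure or sero-surveillance. This is a change of wording and costs nothing.
2. Where suitable stored material exists, estimate the specificity of each antibody assay, including the reference ELISA, on about 200 to 300 sera or plasmas collected before December 2019, split by HIV status where available. The article says that "CIRCB has a biobank dedicated for the storage of well characterised infectious samples collected from heath facilities and within research projects" and that the centre dates from February 2006 and stores serum and plasma. It does not say that pre-2020 aliquots remain, that HIV-negative donors are held, or that consent allows reuse; these need checking.

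The second step needs no new participants. It costs kits and laboratory time for each assay, plus approval for secondary use. Donors from HIV and co-infection work may not represent a surveillance population, and stored sera may differ slightly from fresh ones; the report should say so. If no such sera exist, the first step alone applies.
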